## Abstract

**Background:**

The Happy Life Club™ is an intervention that utilises health coaches trained in behavioural change and motivational interviewing techniques to assist with the management of type 2 diabetes mellitus (T2DM) in primary care settings in China. Health coaches will support participants to improve modifiable risk factors and adhere to effective self-management treatments associated with T2DM.

**Methods/Design:**

A cluster randomised controlled trial involving 22 Community Health Centres (CHCs) in Fengtai District of Beijing, China. CHCs will be randomised into a control or intervention group, facilitating recruitment of at least 1320 individual participants with T2DM into the study. Participants in the intervention group will receive a combination of both telephone and face-to-face health coaching over 18 months, in addition to usual care received by the control group. Health coaching will be performed by CHC doctors and nurses certified in coach-assisted chronic disease management. Outcomes will be assessed at baseline and again at 6, 12 and 18 months by means of a clinical health check and self-administered questionnaire. The primary outcome measure is HbA1c level. Secondary outcomes include metabolic, physiological and psychological variables.

**Discussion:**

This cluster RCT has been developed to suit the Chinese health care system and will contribute to the evidence base for the management of patients with T2DM. With a strong focus on self-management and health coach support, the study has the potential to be adapted to other chronic diseases, as well as other regions of China.

**Trial Registration:**

Current Controlled Trials ISRCTN01010526

## Background

Over the last decade, chronic illness prevention and management has emerged as a critical issue in the health of populations. The World Health Organisation (WHO) has estimated that cardiovascular diseases (CVD), type 2 diabetes mellitus (T2DM), chronic respiratory diseases and cancers account for 60% of all global deaths [1]. This figure represents 35 million deaths annually and is expected to increase by 17% over the next 10 years [1]. Yet many of these conditions are partly influenced by modifiable risk factors; smoking, sedentary behaviour, low consumption of fruit and vegetables and high alcohol consumption [2]. The WHO have estimated that up to 80% of new cases of T2DM, CVD, and stroke could be prevented by reducing behavioural risk factors and have called for '... interventions to reduce the main shared modifiable risk factors for noncommunicable diseases: tobacco use, unhealthy diets, physical inactivity and harmful use of alcohol.' [1]. The Happy Life Club™, described in this paper, is one such intervention, and utilises health coaches trained in behavioural change principles and motivational interviewing (MI) techniques to address the management of T2DM. Health coaches aim to support participants to improve modifiable risk factors and adhere to effective self-management treatments associated with T2DM. The current paper will present details of the study design and research protocols of the Happy Life Club™ which will be implemented in primary care settings in China.

T2DM is among the most serious health problem affecting the population in China and poses a significant public health issue for the community [3]. As a result of economic development in the past two decades, the Chinese population has experienced marked changes in lifestyle. For example, between 1992 and 2002 the combined prevalence of overweight and obesity increased from 14.6% to 21.8% [4], and physical activity among Chinese adults fell by 32% over the period 1991 to 2006 [5]. These changes have been associated with the increases chronic diseases such as T2DM and CVD [3,4]. The Fourth National Health Service Survey, conducted in 2008 by the China Ministry of Health, revealed that cases of T2DM and hypertension have more than tripled over the previous decade [6]. Recently published data reveal that the age-standardised prevalence of total diabetes (which included both previously diagnosed diabetes and previously undiagnosed diabetes) and pre-diabetes were 9.7% and 15.5% respectively, accounting for 92.4 million adults with diabetes and 148.2 million adults with pre-diabetes [7]. According to the International Diabetes Federation, these latest prevalence figures will mean healthcare expenditure on diabetes in China this year will increase by at least US$1.9 billion, reaching a total of US$6.9 billion [8]. In addition, China has a rapidly ageing population, largely driven by the one child policy, with the associated potential increased burden of chronic diseases [9]. By 2040 around 25% of China's population will be aged 65 years and over [10].

In urban China, the health care system features three levels of health providers: community health, district hospitals, and tertiary teaching hospitals. The majority of outpatient care is provided by Community Health Centres (CHCs) and their affiliated community health stations (61.8%) [11]. Primarily owned and managed by the government, the primary role of these community health services is to provide public health, essential medical treatments, preventive health care, and health education to local communities [12]. On average, Chinese residents access community health services 4.4 times per year, with individuals aged 60+ years accessing community health services 7.3 times per year [13]. Patients with T2DM are predominantly managed by doctors at CHCs and the majority of patients incur out-of-pocket expenses for both medical and pharmaceutical services. However, there is a growing recognition from the Chinese government of the need to adopt best-practice medical management, including the provision of diabetes self-care education and the promotion of healthy lifestyle choices [14].

In most countries, T2DM is managed in primary care settings and clinical practice guidelines recognise the importance of a structured and systematic approach that involves a medical care team, including doctors, nurses and dietitians, as well as patients in the management of the condition [15]. As lifestyle changes are fundamental to the management of T2DM [16], health care teams require skills in both counselling and behaviour change in order to work with the patient to achieve their goals and ensure adherence to recommendations [17]. However skills in these areas are often limited and it has been recognised that training in tailored approaches to counselling, provided by techniques such as MI [18], have the potential to improve lifestyle changes in people with chronic illnesses [19]. MI is a directive, client-centred counselling style for eliciting behaviour change by helping clients to explore and resolve ambivalence [18]. It involves a complex set of skills that grow and develop through disciplined practice with feedback and coaching from a knowledgeable guide [20]. MI has been shown to be effective in improving glycaemic control in adults with T2DM [21]. The Happy Life Club™ uses MI delivered by health coaches to assist patients with diabetes in the management of their condition.

### Development of the Happy Life Club™

The Happy Life Club™ is an adaptation of a diabetes intervention delivered in Australia, the Good Life Club [22]. Patients with T2DM were referred to the Club by their doctor and once enrolled received monthly telephone coaching by a health care practitioner trained in MI and behaviour change techniques. The Happy Life Club™ similarly uses telephone coaching and in addition has face-to-face coaching by nurses and doctors trained in MI and behaviour change techniques. Our evaluation of the Good Life Club revealed that participants preferred to have face-to-face coaching at least in the early phases of the intervention [23].

A pilot study was carried out in five community health stations in the Fangzhuang district of Beijing, China [24]. To assess the feasibility and implementation of the Happy Life Club™ trial design, participants were randomly allocated into either:

1. Intervention group where patients with T2DM received 12 months of health coaching in combination with usual care.

2. Control group where patients with T2DM received usual care only.

In total, one hundred participants (20 per community health station) aged 50 years and over were recruited into the study. Participants in the intervention group received a maximum of 19 telephone coaching sessions and 18 face-to-face coaching sessions over the 12 month period. In the first two months of the intervention, participants received two face-to-face coaching sessions lasting 30 minutes per session and four telephone contacts lasting 20 minutes per session. The frequency of contact decreased over the 12 month period as participants gained skills and confidence in self-management. The pilot study enabled the established trial management procedures, piloted questionnaires, measured compliance and standardised operating procedures. Results from analyses of the pilot study demonstrated that participants in the intervention group had significant improvements in triglyceride levels. Improvements were also made in blood glucose monitoring, adherence to medication, physical activity and psychosocial distress.

### Trial objective

To determine the effectiveness of the Happy Life Club™ intervention in improving the HbA1c level and metabolic, physiological and psychological profiles of participants at 6, 12 and 18 months compared with usual care.

## Methods

### Trial design

The current study is an evaluation of the Happy Life Club™, through an 18-month cluster randomised controlled trial (RCT). Cluster randomised sampling of community health stations was chosen to minimise experimental contamination between the control and intervention participants [25]. The Happy Life Club™ trial is managed jointly by Monash University - Melbourne, Peking University - Beijing and Fengtai Health Bureau - Beijing. The study protocol was approved by Monash University Human Research Ethics Committee.

CHCs will be randomly allocated to one of two groups:

1. Intervention group where patients with T2DM receive 18 months of health coaching in combination with usual care.

2. Control group where patients with T2DM receive 18 months of usual care only.

### Study population & setting

The study will be implemented at CHCs in the Fengtai District of Beijing, China. This district is a large residential community in southwest Beijing with a population of 1.823 million residents and an average life expectancy of 78.7 years [26]. Conveniently located within communities, CHCs deliver primary health care and basic health care to Fengtai residents. The socio-demographic profile of residents in Fengtai varies according to geographic location. West Fengtai is predominantly a regional/rural area; Central Fengtai is a residential suburban area; and East Fengtai is an urban area located near downtown Beijing.

### Recruitment process

Figure 1 details the recruitment and randomisation of CHCs and patients into the study. As shown in Figure 1, a list of T2DM patients from each CHC will be generated prior to CHC randomisation, and eligible patients will be contacted by mail.

**Figure 1 F1:**
[figure not shown]
**Flow chart of the recruitment and randomisation of community health centres and participants**.

CHCs will then be randomly assigned to the control (usual care) or intervention group (usual care plus health coaching). Upon recruitment, participants will receive a baseline assessment. All participants will receive clinical assessment at 6, 12 and 18 months.

### Participants

An independent person at each participating CHC will identify eligible participants from the patient health records maintained at each site. Patients with T2DM will be eligible to participate if they are aged 50 years and over, reside in the Fengtai district, have an established health record and are receiving care at one of the participating CHCs. Exclusion criteria include the inability to understand and provide informed consent (e.g., people with cognitive problems), or a medical condition that precludes adherence to recommendations (e.g., end stage cancer, severe mental illness). All eligible participants will be sent an explanatory statement and consent form, either by mail to their home address or in person at their next community health visit. Those wishing to participate in the study will be asked to return the signed consent form to their CHC. All consenting participants will be allocated an ID number will be asked to return to their CHC for the baseline clinical health check. As participation in the trial will require no payment by the participants, we expect that this will provide a high incentive as patients are usually required to pay for CHC visits in China.

### Community Health Centres

As a result of extensive consultation with both the Beijing Health Bureau and Fengtai Health Bureau, it has been agreed that all CHCs located in the Fengtai district will participate in the study, that is, 22 CHCs will be involved in the implementation of the study. An information session will be conducted for all CHC staff, which will thoroughly explain the administrative and implementation aspects of the study. In addition, a member of the research team will visit each CHC to meet with staff and answer specific questions in relation to the study.

### Randomisation

Randomisation will be performed prior to baseline assessment of participants and CHCs will be the unit of randomisation. A member of the research team, blinded to CHC identity, will be responsible for central randomisation. Firstly, CHCs will be stratified by geographical location (east, central, and west) in order to achieve balanced groups according to socioeconomic status. Following stratification, CHCs will be randomly allocated into the control or intervention groups using block randomisation by computerised random allocation software.

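### Community health centres are randomised before baseline, and nothing in the article keeps allocation from staff and patients until consent and the baseline check are complete

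*Protocol article*

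**What the plan says.** The Randomisation section fixes one part of the order: "Randomisation will be performed prior to baseline assessment of participants and CHCs will be the unit of randomisation". The other steps are spread over several sections of the protocol article.

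- **Recruitment process:** "a list of T2DM patients from each CHC will be generated prior to CHC randomisation, and eligible patients will be contacted by mail". The text after Figure 1 says that CHCs are then assigned to an arm, and continues: "Upon recruitment, participants will receive a baseline assessment".
- **Abstract, Methods/Design:** randomisation is described as "facilitating recruitment of at least 1320 individual participants with T2DM into the study".
- **Participants:** the explanatory statement and consent form reach patients "either by mail to their home address or in person at their next community health visit". Signed forms go back to the patient's own CHC, and consenting patients return there for the baseline check. No time limit relative to randomisation is given.

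The article also states safeguards. An independent person identifies eligible patients from health records. Randomisation is central, by someone who does not know which CHC is which. Physical measurements and blood samples are taken by blinded Peking University staff, and the laboratory is blinded. The questionnaire is self-administered.

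**The concern.** In a cluster trial, randomising the clusters balances the patients only if later entry does not depend on the arm. Here the arms offer visibly different things: 18 months of coaching by CHC doctors and nurses, or usual care. If staff or patients know the arm while consent is being sought, or before the patient comes back for baseline, the two arms may enrol different kinds of patient. Readiness to change is an obvious candidate, and it is related to how HbA1c moves afterwards. Baseline answers on distress, self-efficacy and self-care may also shift once the arm is known. A multilevel model handles the correlation within CHCs but does not undo selective entry, and no later analysis can fully repair it.

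**Working it through.** **1. Order of steps.**

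| Step | What the article fixes |
|---|---|
| Patient list | Before randomisation (Recruitment process) |
| Mail contact | Same sentence as the list, so before randomisation on a plain reading |
| In-person contact | Next CHC visit, no time limit (Participants) |
| Consent | Not placed. The Abstract and the text after Figure 1 suggest that recruitment follows randomisation; the mail contact suggests that some consent may precede it |
| Baseline check and questionnaire | After randomisation (Randomisation) |

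Even a patient who consented early must still attend a baseline check that follows allocation.

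**2. What each safeguard protects.** Listing from records protects who is invited, not who consents or attends. The blinded central randomiser protects the draw, not enrolment after it. Blinded assessors and laboratory protect the measurement of HbA1c, not the mix of patients measured. None covers the questionnaire.

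**3. The plan's own figures (Sample size).** An effect of 0.32 SD, 5% two-sided and 80% power need 154 per group, 308 in total, against 306 stated. With 60 per CHC and 20% attrition there are 48 completers per CHC. The design effect at ICC 0.05 is 1 + 47 × 0.05 = 3.35, and 306 × 3.35 / 0.8 = 1281, close to the stated 1320. The sample size is not in question; these are the inputs for step 4.

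**4. Size under the planned test.** The Statistical analysis section puts the arm effect in the trajectory. I computed the generalised least squares estimate of the 18-month arm difference in slope, with no arm term in the intercept.

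From the plan: visits at 0, 6, 12 and 18 months (t = 0, 1/3, 2/3, 1), 11 CHCs per arm, 48 completers each, ICC 0.05. Assumed: within-person correlation r of 0.5 to 0.7, cluster variance of 18-month slope (τc²) 0 to 0.05, participant variance of slope (τp²) 0 to 0.2, total baseline variance 1.

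Covariance of a CHC's four visit means: V = 0.05·11′ + τc²·tt′ + [(r − 0.05)·11′ + τp²·tt′ + (1 − r)·I] / 48.

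One-sided error with no true effect: 1 − Φ(1.645 − b/SE), where b is the bias in the 18-month effect.

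| r | τc² | τp² | SE | b from constant 0.10 SD shift | Error | Error if 0.10 SD acts on change |
|---|---|---|---|---|---|---|
| 0.5 | 0 | 0 | 0.056 | 0.014 | 8.1% | 55% |
| 0.7 | 0 | 0 | 0.044 | 0.008 | 7.2% | 73% |
| 0.5 | 0.05 | 0.2 | 0.114 | 0.014 | 6.4% | 22% |
| 0.7 | 0.05 | 0.2 | 0.109 | 0.008 | 5.8% | 23% |

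A constant shift therefore gives about 6-8%, and exactly 5% if the model has its own intercept for each arm. A shift in change enters the effect in full (b = 0.10). Its error is lowest, at about 20%, when slopes vary most between CHCs; a cluster slope variance above 0.05 would lower it further.

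**5. Single-endpoint comparison, for contrast.** Effective n per arm = 11 × 48 / 3.35 = 157.6, and SE = √(2/157.6) = 0.113. A 0.10 SD difference then gives 1 − Φ(1.645 − 0.10/0.113) = 22%. This is not the planned test.

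**The case against.** The strongest reply is that the article already protects the primary outcome. The list precedes randomisation, someone independent draws it up, and HbA1c is measured and analysed blind. On a plain reading the mail contact also precedes allocation. The explanatory statement is not shown, and nothing says that it differs by arm. Participation is free in both arms, and there is no HbA1c entry threshold to drive different regression to the mean. Figure 1, which may settle the order, is not available in the text reviewed.

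Much of this stands. A reader might infer that CHCs are randomised before patients consent; the article does not establish that, and some or all consents may come first. A reader might also take 22% as the error of the planned test under a baseline imbalance. That figure belongs to a single-endpoint comparison, and the trajectory test absorbs most of a constant shift. Altered self-report touches only questionnaire outcomes, which are secondary and tested at p < 0.001.

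What does not fall is the path itself. Baseline follows allocation by explicit statement, consent may be sought in person without a time limit, and no concealment up to that point is described. Blind measurement of HbA1c does not help if different patients come to be measured.

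**Conclusion.** The point holds in a limited form. The order that the article fixes leaves consent and baseline attendance open to knowledge of allocation, and the stated safeguards do not prevent this. It does not follow that selection will occur, or in which direction. Selection favouring intervention raises the false-positive rate; the reverse would hide benefit, and a bias of −0.10 SD would make a true 0.32 SD appear as 0.22 SD.

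The documents give no size. With an assumed 0.10 SD, a constant baseline shift raises one-sided error from 5% to about 6-8%, while selection acting on 18-month change raises it to at least about 20%, and well above that if slopes vary little between CHCs. These results rest on the assumed correlation and slope variances, complete balanced data at 48 per CHC, and a normal approximation. The change is worth making because it is cheap and because the bias cannot be removed afterwards.

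**What to change.** Amend the Randomisation section to say that allocation is disclosed to a CHC, its staff and its patients only after that CHC's participants have consented and completed the baseline check and questionnaire. The central randomiser may draw the allocation earlier, provided it is not released. Bring the Abstract, the Recruitment process section and the text after Figure 1 into line, so that the place of consent is stated once and consistently.

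If this is not feasible, have recruiters who do not know the allocation work from the list made before randomisation, and report by arm the numbers approached, consenting and attending baseline. That limits the bias and makes it visible, but does not remove it.

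The change re-orders existing steps and leaves the sample size as it is. The cost is that coach training and coaching in intervention CHCs start later, with a somewhat longer gap between the earliest baselines and the first session. The documents do not allow that delay to be quantified.

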### Sample size

Based on conventional methods for estimating a sufficient sample size in a randomised trial with two conditions, and assuming that individuals are randomised to conditions, the number of participants needed is determined mainly by three parameters [27]. These parameters are: (1) the tolerable Type I error rate (assuming the null hypothesis); (2) the desired level of statistical power (assuming the alternative hypothesis); and (3) an anticipated effect size for a relevant test statistic (e.g., standardised mean difference). Consistent with general conventions, [27] the current study specified a 5% Type I error rate as tolerable and required 80% power. The primary outcome measure was glycosylated haemoglobin (HbA1c), measured on a continuous scale, and a recent meta-analysis evaluating psychological interventions to improve glycaemic control in patients with T2DM [21] indicates an expected standardised effect of 0.32 across studies. This was the anticipated effect size estimate specified in the current investigation. Based on these parameters, and using the G*Power 3.1 program [28] to conduct calculations, it was ascertained that a sample size of *n *= 306 (153 per group) would be sufficient to detect an effect size of 0.32 with 80% power, while maintaining 5% Type I error.

As noted, the sample size calculations reported above assume that individuals are randomised to groups. In contrast, cluster randomisation, as used in the current study, is associated with less statistical power; especially when individuals within clusters are similar [29]. This degree of similarity is quantified by the Intra-Class Correlation (ICC) coefficient, which can then be used, along with estimates of the average cluster size (in terms of number of participants per cluster) [30] to calculate an adjusted sample size; inflated to yield the same level of statistical power as if individual randomisation was used [29]. Only a limited number of clusters were available to the current study, and estimates were calculated assuming this fixed number (*k *= 22). As described by Campbell et al. (2000), ICCs for outcome variables in primary care research are generally lower than 0.05, and this value was also specified in the adjusted calculations. A sample size calculator for cluster-randomised trials is available [29] and was used to estimate the required sample size given cluster randomisation. Allowing for a participant attrition rate of 20%, it was estimated a total sample of *n *= 1320 would be required to achieve at least 80% power, while maintaining 5% Type I error. This figure reflects 60 patients per CHC (cluster), and 660 per intervention group.

